### Participant Timeline

The full study timeline is approximated to take 20 weeks (Table 2). Possible schedules for participation will vary per participant; however, assessments will be within ± 1 week from the suggested dates for accommodations (Tables 3 and 4).

### Sample Size

No previous sample data exist for this type of study that would enable sample size calculations. Data from a study on finger muscle control in children with dystonic CP with a mean difference effect size for within-subjects designs of dz=2.98, alpha=.05, and power=0.8 yields a required sample size of n=4 in each comparison group [26]. Given the wide age range and motor impairment characteristics in the eligibility criteria for this study, we propose a sample size of n=17 with a total number of 68 participants. We expect a 25% attrition rate that will approximately yield a total of 13 participants per group. We consider that this number is a conservative estimate for a randomized controlled trial in the pilot phase.

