### Trial Design

We will conduct paired *t* tests on movement outcomes for the CP and TD groups independently. In case of non-normality, nonparametric techniques will be used. Differences before and after as well as before and follow-up will be obtained on the primary outcome measure: smoothness of movement. Differences will also be calculated on secondary outcomes for exploratory purposes. The primary outcome measure will be the smoothness index of the accelerometry signals of sensors placed on the upper limb segments. Secondary outcomes include the interaction force with the robot and a battery of clinical tests and a quantitative measure of spasticity. The study is powered for the main outcome. The desired allocation will be 1:1, with 1 participant in the control group for every participant in the intervention group for both CP and TD participants.

In the application presented here, the VR environment follows a prescribed remapping based on principal component analysis of force data generated from people with typical movement control [22,23]. Participants will, therefore, be asked to produce efforts in directions of high variance that are associated with performance of typically developed adults.

This intervention will not be incorporated into a broader health care program at this time.

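### The statement that the study is powered for its main outcome is unsupported: the only effect size is a within-subject value from a finger-muscle study, and 13 per arm gives 80% power only for a between-arm difference of about 1.15 SD

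*Protocol article*

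**What the plan says.** Trial Design declares, without qualification: "The study is powered for the main outcome". That section names smoothness of movement as the primary outcome and sets 1:1 allocation to intervention or no-intervention control within the CP and TD groups.

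Sample Size opens with: "No previous sample data exist for this type of study that would enable sample size calculations". It then takes an effect size from elsewhere ("Data from a study on finger muscle control in children with dystonic CP") and reports that an "effect size for within-subjects designs of dz=2.98, alpha=.05, and power=0.8 yields a required sample size of n=4 in each comparison group". Citing the wide age range and motor impairment, it continues: "we propose a sample size of n=17 with a total number of 68 participants". On losses it says: "We expect a 25% attrition rate that will approximately yield a total of 13 participants per group". It closes: "We consider that this number is a conservative estimate for a randomized controlled trial in the pilot phase".

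Trial Design and Statistical Methods name paired *t* tests on before/after and before/follow-up differences, run separately in the CP and TD groups, with Bonferroni corrections where needed. Neither section names a test of intervention against control. The article gives no SD or expected effect for the smoothness index.

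**The concern.** A claim that a trial is powered for an outcome needs an effect size for that outcome and for the comparison that answers the objective. The borrowed value fails on both counts.

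- **Outcome.** It concerns finger muscle control. The primary outcome here is a smoothness index of upper-limb movement.
- **Contrast.** It is a within-subject effect. The objective is the effect of the intervention, and the trial randomises against a no-intervention control to isolate it.

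The claim also conflicts with the opening sentence of Sample Size. If no data allow a calculation, the study cannot be said to be powered on the strength of one.

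At stake is how the primary result is read. If a non-significant finding is reported from a study described as powered, the reader needs to know which effects the sample could have detected.

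**Working it through.** **Inputs from the article.** dz=2.98, alpha 0.05 and power 0.8; 17 enrolled per cell in four cells (CP or TD, intervention or control); 25% attrition; 1:1 allocation. Sidedness is not stated, so two-sided is assumed. No SD is given, so between-arm differences are in SD units of the quantity compared.

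**1. The plan's n=4.** Paired *t* test, df = n − 1, noncentrality dz·√n:

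- n=3: 2.98 × √3 = 5.16, power 74.1%
- n=4: 2.98 × √4 = 5.96, power 96.5%

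The smallest n with at least 80% power is 4, so the figure reproduces. A one-sided test would give n=3 (92.8%), so two-sided is the reading that matches. A two-sample test with d=2.98 would also give 4 per group (77.7% at 3, 93.6% at 4).

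**2. Evaluable numbers.** 17 × 0.75 = 12.75, about 13 per group, as stated.

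**3. Detectable between-arm difference.** Two-sample *t* test, df = 2n − 2, noncentrality d·√(n/2), solved for 80% power. For 13 per arm the normal approximation is (1.960 + 0.842) × √(2/13) = 1.10 SD; the exact noncentral-*t* solution is 1.145 SD.

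| Evaluable per arm | Alpha | Detectable difference |
|---|---|---|
| 13 | 0.05, two-sided | 1.145 SD |
| 12 | 0.05, two-sided | 1.20 SD |
| 17 | 0.05, two-sided | 0.99 SD |
| 13 | 0.025, two-sided | 1.28 SD |
| 13 | 0.05, one-sided | 1.00 SD |

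The 0.025 row assumes a Bonferroni split over the two time contrasts. The article says only that corrections apply as needed.

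**4. Power with 13 per arm, two-sided 0.05.** 23% at 0.5 SD, 50% at 0.8 SD, 69% at 1.0 SD and 80.3% at 1.15 SD.

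**5. Precision.** The 95% CI half-width is t(0.975; 24) × √(2/13) = 2.064 × 0.392 = 0.81 SD.

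**6. Baseline adjustment.** The detectable difference in SDs of the outcome itself is about 1.145 × √(1 − r²), which is 0.99 SD at r = 0.5 and 0.82 SD at r = 0.7. Both correlations are assumptions.

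**7. The test the article names.** A paired test within one arm of 13 has 80% power for dz of about 0.85.

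**The case against.** The strongest defence is that the article plans paired tests, and a within-subject dz is the right kind of input for a paired test. With 13 children that test detects dz of about 0.85, far below 2.98. This stands in part: the 1.15 SD figure belongs to the comparison that the randomised design calls for, not to a test the article names. It does not rescue the power statement. A before/after test within one arm makes no use of the control group, and even for that test the article offers no dz for smoothness.

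A second defence is disclosure. Sample Size admits the lack of data, goes well above n=4 because of heterogeneity and speaks of a pilot phase. Limitations mentions the small sample. This softens the fault. However, the Limitations remark concerns generalization, and the sentence in Trial Design carries no caveat.

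Three stronger readings are tempting but not supported:

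- *The sample-size arithmetic is wrong.* It is not; both n=4 and the 13 after attrition reproduce.
- *The trial lacks power for any moderate or large effect.* Power is at least 80% from about 1.15 SD upward, or from about 0.99 SD if all 17 per arm are evaluable. The shortfall concerns smaller effects, including 0.8 SD, which is conventionally called large.
- *A null result will be taken as proof of no effect.* That is a risk of the wording; given the pilot label, it is not a certainty.

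The absence of a worked power figure for each corrected alpha level is also no fault in itself, since a condensed article may leave it to the full documents.

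**Conclusion.** The point holds as a flaw in the sample-size justification. The unqualified power statement in Trial Design conflicts with the opening of Sample Size and rests on an effect that matches neither the primary outcome nor the randomised contrast.

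The size of the gap can be stated. A between-arm comparison in children with CP reaches 80% power only at about 1.15 SD and would miss a true difference of 0.8 SD about half the time. This assumes 13 evaluable per arm, two-sided 0.05, a two-sample *t* test, and an SD that is that of the quantity compared, such as the change score. Full retention or a useful baseline covariate would lower the threshold; the Bonferroni split over two time contrasts would raise it. A reader might infer that N=68 must be increased. The documents do not require that of a pilot; what needs correcting is the claim made for that number.

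**What to change.** 1. In Trial Design, delete the sentence declaring the study powered for the main outcome.
2. In Sample Size, stop presenting dz=2.98 and n=4 as the justification. Say that N=68 is a pilot size set by judgement, given the absence of data on smoothness.
3. In Trial Design and Statistical Methods, name the between-arm comparison of change in smoothness in children with CP as the primary analysis. Without this, a between-arm power figure would not match the planned paired tests.
4. Add to Sample Size, for example: *For the between-arm comparison of change in smoothness in children with CP, 13 evaluable children per arm give 80% power (two-sided 0.05) for a difference of about 1.15 SD of the change score, or about 0.99 SD if all 17 per arm are evaluable; the detectable difference is smaller if baseline adjustment reduces the variance. The estimate will be reported with its 95% CI.*

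N=68 is unchanged and no participants are added. The costs are rewording, naming the between-arm analysis and a less favourable stated power. The article says the trial has not started, so the change can precede enrolment.

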### Recruitment

The participants will be neither students nor employees of the research team personnel. We intend to recruit participants from the Central Illinois community. Physicians involved in the experiment from the Children’s Hospital of Illinois/OSF Saint Francis Medical Center will assist in referring participants and may distribute flyers with contact information regarding the study. In addition, participants will be recruited through posted flyers, advertisement in the Daily Illini, E-week, local newspapers, and laboratory websites. Once participants’ parent or guardian receives information about the study, they will have the option to contact the principal investigator as indicated in the study information flyer. We are not accessing patient records for recruitment or Illinois schools. The final decision on inclusion will be made by the principal investigator in accordance to the inclusion and exclusion criteria of the experiment.

During the initial contact interview, research assistants will read a script describing the study and, if interested, parents or guardians will be provided with the participant medical form, to be completed by the parent or guardian and physician, and the consent form. A model consent form is provided in the Multimedia Appendix 1. Screening materials will be kept for participants that enroll in the study and destroyed for those that do not meet the criteria or decide not to enroll. A schematic diagram is included (Figure 3).

**Figure 2 figure2:**
[figure not shown]
Royal Academy of Dance first port de bras. From left to right: en bas, first position, second position, and en bas. Participants will be asked to move through these positions during assessment 7 to measure muscle activity patterns and smoothness of movement.

**Table 2 table2:** Full study timeline. Experiment tasks are divided into weeks.

Time (weeks)	1	2	3	4	5	6	7	8	9 to 14	15 to 20
Recruitment and enrollment	✓^a^	✓	—^b^	—	—	—	—	—	—	—
Baseline assessments	✓	✓	—	—	—	—	—	—	—	—
Intervention period	—	✓	✓	—	—	—	—	—	—	—
Postassessments	—	✓	✓	—	—	—	—	—	—	—
1-month follow-up	—	—	—	—	—	✓	✓	—	—	—
Data processing	—	—	✓	✓	✓	✓	✓	✓	✓	—
Data analysis	—	—	✓	✓	✓	✓	✓	✓	✓	✓

^a^✓ corresponds to times when activity occurs.

^b^Empty cells indicate times when activity is not expected to occur.

**Table 3 table3:** Possible schedule 1. Interventions in this schedule will take place over a period of 2 weeks with days between. Assessments will take place over 2 days. This schedule is subject to change based on the participants’ availability.

Time (weeks)	1	2	3	4	5	6	7
Saturday	Assess	—^a^	Assess	—	—	—	Assess
Sunday	Assess	—	Assess	—	—	—	—
Monday	Game	Game	—	—	—	—	—
Tuesday	—	—	—	—	—	—	—
Wednesday	Game	Game	—	—	—	—	—
Thursday	—	—	—	—	—	—	—
Friday	Game	Game	—	—	—	Assess	—

^a^Empty cells indicate no activity.

**Table 4 table4:** Possible schedule 2. Interventions in this schedule will have no days between sessions. Assessments will take place over 2 days. This schedule is subject to change based on the participants’ availability.

Time (weeks)	1	2	3	4	5	6	7
Saturday	Assess	Game	—^a^	—	—	Assess	—
Sunday	Assess	Assess	—	—	—	Assess	—
Monday	Game	Assess	—	—	—	—	—
Tuesday	Game	—	—	—	—	—	—
Wednesday	Game	—	—	—	—	—	—
Thursday	Game	—	—	—	—	—	—
Friday	Game	—	—	—	—	—	—

^a^Empty cells indicate no activity.

**Figure 3 figure3:**
[figure not shown]
Standard Protocol Items: Recommendations for Interventional Trials (SPIRIT) flow diagram of participants. CP: cerebral palsy; DIS: Dyskinesia Impairment Scale; MSRT: Montreal Spasticity Rating Test; PT: physical therapy; QUEST: Quality of Upper Extremity Skills Test; sEMG: surface electromyography; SCUES: Selective Control of the Upper Extremity Scale; WHODAS 2-CY:World Health Organization Disability Assessment Schedule II-Children and Youth.

**Table 5 table5:** Participant group allocation. All participants will be divided into intervention and control groups.

Participants	Intervention (n=34), n (%)	No intervention (control; n=34), n (%)	Total (N=68), n (%)
Children with cerebral palsy	17 (50)	17 (50)	34 (50)
Typically developing children	17 (50)	17 (50)	34 (50)

### Allocation

After the initial contact interview, assessment of inclusion and exclusion criteria, and completion of the consent and assent forms, the participant will be allocated to a control or intervention group using a blocked randomization method (Table 5). The block sizes and randomized sequences will be hidden from those who enroll or allocate participants to prevent predictability of the next assignment. Allocation will be concealed by using sequentially numbered, opaque, sealed envelopes. Different members of the research team will allocate the sequence, enroll participants, and assign them to groups.

### Blinding

Research team members administering clinical assessments will be blinded from participant allocation. Participant’s allocation will not be revealed during the course of the study.

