### Data Collection Methods

All assessors are trained to conduct the assessments for children with and without CP. Outcome data will be collected at assessments.

The Dyskinesia Impairment Scale measures the severity of dystonia and choreoathetosis when an individual is at rest or conducting movement. It was found to show good to excellent reliability and validity [27]. It is also notable that in a 2012 systematic review of measures of dystonia and choreoathetosis, this scale is listed as the only clinical tool that examines choreoathetosis and dystonia in the same scale [28].

The Selective Control of the Upper Extremity Scale is a video-based tool to measure selective control of upper limb tasks. Psychometric analysis shows “comparable validity to other accepted video-based clinical assessment tools for the upper extremity in children with CP” with content validity ratio values indicating substantial agreement for most items [29].

The Quality of Upper Extremity Skills Test is 36 items in length and measures upper limb movement, hand function, and cooperativeness in children with CP. It has been found to be reliable to assess children with CP in the age range of 18 months and 8 years, with increased reliability in children aged up to 12 years [30]. It has also been found to show adequate to excellent validity [31,32].

The Tardieu scale examines spasticity with quantified measures of the responses to stretch reflexes of discrete velocity. This scale shows high test retest and poor to moderate inter-rater reliability; the Tardieu scale performs better than other similar measures, however, indicating it may be more reliable [33].

The Montreal Spasticity Rating Test is a quantitative measure of spasticity that identifies resistance to external forces of stretch tasks. This test identifies the point at which the stretch reflex is activated in a muscle. Documentation on the reliability and validity of this test is unavailable.

The WHODAS II-CY is a self-administered 36-item document that assesses daily issues surrounding health conditions such as illnesses, injuries, and problems with mental health. In a validity study, it was found to show good reliability; however, limitations regarding options for those without significant disabilities were present [34].

Plans to promote participant retention include payment at the end of, or separation from, the study.

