### Statistical Methods

The assessment and training protocols target improvements in selective motor control and amelioration of dystonia. We will conduct paired *t* tests on movement primary and secondary outcomes for the CP and TD groups independently. In case of non-normality, nonparametric techniques will be used. Differences before and after as well as before and follow-up will be obtained on the primary outcome measure: smoothness of movement. Tests on secondary outcomes are for exploratory purposes only. Bonferroni corrections will be applied as needed.

Missing values will be omitted from calculations or corrected for according to standard statistical techniques.

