Images and videos will be stored without personal identifiers associated with the files apart from the image or video itself. If permission is given, these photos could be included in scholarly publications in print and electronic form, which will allow participants’ faces to potentially be visible and recognizable by anyone reading the publications. Photos and videos may also be presented at meetings or conferences without any personal identifiers attached to the photos and videos other than the content itself. Data will be kept with coding and will only be viewable by lab personnel who are associated directly with the maintenance of data for this study.

Video footage with audio will be recorded at all sessions to ensure safety and adhesion to study protocols as well as to record the study. The footage is being taken to ensure the rights of participants and for the researchers alike. By signing the consent and assent forms, authorization is given for the principal investigator and research team to record the participant during participation of the study and to share the footage with the following items if emergencies arise or the research protocol is not properly followed:

The IRBsThe Office of Human Research OversightAuthorized members of the University of Illinois College of Medicine Peoria workforceRepresentatives of the university committee and office that reviews and approves research studiesOffice for Protection of Research SubjectsOther representatives of the state and university responsible for ethical, regulatory, or financial oversight of researchFederal government regulatory agencies such as the Office of Human Research Protections in the Department of Health and Human Services

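### Clinical raters are masked to arm, but the stated test on the exploratory clinical scales is before versus after, where knowing the visit is what can bias a rating

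*Protocol article*

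**What the plan says.** The Blinding section of the protocol article has two sentences, and both concern allocation: "Research team members administering clinical assessments will be blinded from participant allocation", and "Participant’s allocation will not be revealed during the course of the study". Neither mentions the visit, and the first covers people who administer the tests.

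Statistical Methods sets paired t "tests on movement primary and secondary outcomes for the CP and TD groups independently". The contrasts are given there for the primary outcome: "Differences before and after as well as before and follow-up will be obtained on the primary outcome measure: smoothness of movement". Trial Design extends them to the secondary outcomes, which include the clinical battery: "Differences will also be calculated on secondary outcomes for exploratory purposes". Statistical Methods limits their weight: "Tests on secondary outcomes are for exploratory purposes only". Neither section names a comparison of intervention with control.

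Two further statements bear on the remedy. Data Collection Methods says "The Selective Control of the Upper Extremity Scale is a video-based tool to measure selective control of upper limb tasks". Ethics and Dissemination says "Video footage with audio will be recorded at all sessions to ensure safety and adhesion to study protocols as well as to record the study", and in its list of identifiable elements it states that photos and videos contain no close-ups.

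**The concern.** Masking raters to arm makes any drift in scoring common to both arms, and a common drift drops out of a between-arm difference. It stays in full in a within-group before/after difference, because the post scores carry it and the baseline scores do not. The masking and the stated test therefore do not match.

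Raters very probably know the visit. They give the tests in person, and under Interventions the baseline assessment doubles as the eligibility check and precedes allocation. Post and follow-up assessments come on later dates.

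At stake is how a clinical gain would be read. The hypothesis in the Background covers clinical as well as quantitative measures, and the closing Conclusions expect improvement on clinical tests. Drift by raters who share that expectation would look the same as the hoped-for gain in the paired test.

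**Working it through.** **Inputs from the protocol (Sample Size).** dz = 2.98 for a within-subjects design, alpha = 0.05, power = 0.8, stated n = 4. Planned n = 17 per group with 25% attrition.

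**The plan's own figure first.** For a two-sided paired t test, power is P(|T| > t(0.975, n−1)), where T is noncentral t with n−1 degrees of freedom and noncentrality dz·√n.

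- n = 3: noncentrality 2.98·√3 = 5.16, critical value 4.303, power 0.741.
- n = 4: noncentrality 2.98·√4 = 5.96, critical value 3.182, power 0.965.

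The smallest n reaching 0.8 is 4, as stated. The figure is consistent with a within-subject test, which is the frame the protocol names. Completers: 17 × (1 − 0.25) = 12.75, about 13 per group, also as stated.

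**Effect of a rating drift.** Let b be the drift in post scores, in SDs of the change score, with a true change of zero. The documents give no value for b, so 0.2, 0.3 and 0.5 are assumptions. The probability of a significant paired test uses the same formula with noncentrality b·√n. For n = 13 the critical value is 2.179 at alpha 0.05 and 3.055 at alpha 0.01. The 0.01 level assumes that Bonferroni is applied over the five clinical and spasticity measures (0.05/5); the protocol says only that corrections apply as needed.

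| b (assumed) | b·√13 | alpha 0.05 | alpha 0.01 |
|---|---|---|---|
| 0 | 0 | 5% | 1% |
| 0.2 | 0.72 | 10.2% | 2.6% |
| 0.3 | 1.08 | 16.9% | 5.1% |
| 0.5 | 1.80 | 38.2% | 15.6% |

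If the two CP arms were pooled (26 completers), the rates at alpha 0.05 would be 17%, 31% and 69%. The text on analysing CP and TD independently permits pooling. It is the less plausible reading, because Sample Size speaks of comparison groups of 13, so I do not rely on it.

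**The same drift in a between-arm test.** A simulation (100,000 runs, 13 versus 13, t test on change, equal drift in both arms) rejects in 4.9% to 5.0% of trials for b = 0, 0.3, 0.5, 0.8 and 1.0. The drift cancels.

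**The case against.** The strongest objection is that the root defect lies in the test, not in the masking. Arm masking is the right safeguard for a randomised comparison, and a between-arm test of change would hold its level under any common drift. This stands, and the fix below uses it. The within-arm changes would still be distorted wherever they are reported.

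Four limits also stand.

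- The clinical scales are labelled exploratory, and the primary outcome comes from instruments. A reader might infer that the trial's main conclusion is exposed to rater expectation. The documents do not support that: no rater's score enters the smoothness index.
- Visit unmasking is inferred from silence in a condensed article. The inference is strong for tests given in person, but no sentence says that raters know the visit.
- A reader might infer that someone unmasked scores the Selective Control video. No passage says so. The wording simply does not reach a scorer who is not also the administrator.
- A reader might infer that filming every session makes visit masking available for all scales. The film is general session footage without close-ups. The Tardieu and Montreal tests rest on responses during manual stretch, which such film cannot be assumed to show.

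On size, a rater masked to arm in a 1:1 trial knows that half the children were not trained, which may weaken expectation. Bonferroni, if applied, lowers the rates but does not remove the bias.

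**Conclusion.** The point holds for the exploratory clinical scales only. The masking is to arm, the stated contrast is before versus after, and for that contrast knowledge of the visit is the source of rater bias. If post scores drift by 0.2 to 0.5 SD of the change score with no true effect, a paired test on 13 completers is falsely significant in 10% to 38% of trials at two-sided 0.05, or 3% to 16% at 0.01. These rates illustrate the mechanism. They do not estimate the drift in this trial, whose size the documents do not give. This is a modest, worthwhile correction, and cheap now because the trial has not started.

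**What to change.** 1. In Blinding, extend the rule to whoever scores the video, and add masking to visit for video-scored outcomes.
2. Score the Selective Control scale from coded clips, in random order of visit, after the last follow-up, by the existing blinded assessor masked to arm and visit.
3. Do the same for items of other observational scales only where the existing film proves adequate. Leave the Tardieu and Montreal tests scored live.
4. In Statistical Methods, state that for scales scored live any claim of clinical gain rests on the difference in change between intervention and control within CP. This cancels drift common to both arms, provided the arm masking holds.

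Cost: a coding and shuffling step, with no new visit, procedure or staff. Selective Control scores would be available only after follow-up, and live-scored scales would keep some distortion in their within-arm changes.
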